## Abstract

As stroke survivors often manifest not only physical dysfunction but also cognitive impairment, interventions that address both physical and cognitive aspects may be beneficial for individuals with chronic stroke. However, a randomized clinical trial (RCT) examining the effects of physical–cognitive telerehabilitation exergaming across physical and cognitive domains in chronic stroke survivors remains scarce. Therefore, this study aims to investigate the effectiveness of the web-based physical–cognitive telerehabilitation exergaming on the physical and cognitive performance of chronic stroke survivors as compared to control. A two-arm RCT with a blinded assessor will be conducted. Fifty-two participants will be randomly assigned to either the intervention or the control group. Participants in the intervention group will receive a 12-week training program, whereas those in the control group will continue with usual care. Motor function, gait speed, balance, fall risk, muscle power, weight distribution, body composition, global cognition, executive function, attention, memory, as well as enjoyment will be assessed. Existing evidence has established the health benefits of physical–cognitive exergaming. It is expected that a physical–cognitive exergaming program may further exhibit positive effects on both physical function and cognition beyond the results of usual care. In addition, incorporating physical–cognitive training into a web-based telerehabilitation program may improve adherence and provide a feasible and enjoyable rehabilitation option for individuals with chronic stroke.

## 1. Introduction

Stroke survivors commonly experience muscle weakness, impaired balance, and reduced mobility, which substantially limit activities of daily living, community participation, and functional independence [1]. In parallel with physical dysfunction, cognitive impairments are frequently reported after stroke and contribute to long-term disability [1,2,3]. Previous studies have shown that cognitive impairment affects 27% of stroke survivors at 3 months and 21% at 12 months after stroke and is associated with poorer quality of life and activities of daily living at 1 year [2]. A meta-analysis of 27 studies demonstrated that poststroke cognitive impairment is associated with a 59% increased risk of recurrent stroke and a twofold higher risk of mortality [3]. Therefore, preventing poststroke cognitive impairment among at-risk individuals and promoting health throughout stroke rehabilitation are critical for reducing stroke-related disability.

It has been well documented that physical exercise and physical activity are recommended as an effective non-pharmacological intervention to improve or restore physical function after stroke [4,5]. The therapeutic approach to stroke rehabilitation requires repetitive training combined with continuous modification of training programs to maintain patient engagement and optimize long-term functional outcomes [6]. However, a previous systematic review reported that common perceived barriers to engaging in or continuing physical activity after stroke include lack of motivation, limited access to rehabilitation services, transportation difficulties, and cost, as well as health concerns and stroke-related impairments [7]. In addition, adherence to physical interventions among stroke survivors has been shown to decrease by 30–50% within the first year [8]. To mitigate these barriers, an intervention that supports care delivery and incorporates accessible, safe, and enjoyable elements may facilitate greater physical activity and adherence to regular exercise among stroke survivors. Digital health interventions, including exergaming and telerehabilitation, have been integrated into healthcare, providing accessible and motivating interventions, extending services to underserved areas, and reducing costs and travel burden [9,10]. Research evidence has demonstrated that exergaming has positive effects on balance and functional mobility in chronic stroke survivors [11]. Allegue et al. [12] demonstrated that exergame-based telerehabilitation improved motor function and movement quality after 8 weeks of training. Ballester et al. [13] reported that remotely delivered exergame-based training for upper-limb rehabilitation improved the functional ability of the paretic arm and hand, enhanced maximal finger flexion, and increased neuroplastic changes in stroke survivors. Burgos et al. [14] showed that a digital health intervention incorporating inertial movement sensors and a web-based exergame platform for remote balance training by a physiotherapist improved balance and activities of daily living among stroke survivors after 4 weeks of intervention. In addition to improving physical health, the interactive features of exergaming and gamification enhanced motivation, leading to greater adherence compared with regular exercise and providing an enjoyable and effective approach for stroke patients [15,16,17].

Research evidence has demonstrated that physical–cognitive training benefits not only physical or motor function [18,19,20] but also cognitive and brain health [21,22,23,24]. Previous studies demonstrated that physical and cognitive training improved the cognitive functions and independent living ability of older adults with and without cognitive impairment [21], enhanced executive function in patients with early-stage Alzheimer’s disease [24], and improved balance and gait and reduced fear of falling and fall incidence in patients with cerebrovascular disease [18]. Among stroke survivors, existing evidence suggests that physical and cognitive training is more effective than single-modality interventions or usual care in improving cognitive and functional outcomes after stroke [25,26,27]. A previous randomized controlled trial (RCT) demonstrated that physical and cognitive training improved cognitive function, with cognitive benefits maintained at the 6-month follow-up in stroke survivors [27]. A systematic review and meta-analysis study indicated that physical–cognitive training improved the cognitive function of poststroke cognitive impairment, particularly in the domain of executive function [28]. According to cognitive–motor interference theory, the combination of motor and cognitive tasks places demands on attentional capacity and the integrity of executive functions [29]. A previous study reported that combined motor and cognitive tasks increased task complexity, enhanced brain activation and functional connectivity, and facilitated the engagement of distributed neural networks [30]. Collectively, physical–cognitive interventions may yield synergistic effects and lead to superior outcomes compared with usual care or single-modality training.

To the best of our knowledge, no previous studies have investigated the effects of physical–cognitive training on both physical and cognitive outcomes in chronic stroke survivors, particularly across a comprehensive range of domains, including motor function, gait speed, balance and limits of stability, fall risk, muscle power, and weight distribution, as well as global cognitive function, executive function, memory, and attention. Additionally, there is a limited number of studies that have incorporated physical–cognitive training with web-based exergaming and a gamification approach into telerehabilitation to promote engagement and adherence to exercise. Therefore, this study aims to investigate the effectiveness of the web-based physical–cognitive telerehabilitation exergaming on the physical and cognitive performance of chronic stroke survivors as compared to control. Given the health benefits of combined training and the accessibility of digital health interventions, it is hypothesized that web-based physical–cognitive telerehabilitation exergaming would be beneficial to chronic stroke survivors and may potentially provide greater physical and cognitive benefits than control conditions.

## 2. Materials and Methods

### 2.1. Aims

The purpose of this study is to investigate the effectiveness of the web-based physical–cognitive telerehabilitation exergaming on the physical function and cognitive performance of chronic stroke survivors as compared to the control condition.

### 2.2. Study Design

This study is designed as a two-arm, assessor-blinded randomized controlled trial. The study protocol was developed in accordance with the Consolidated Standards of Reporting Trials (CONSORT) guidelines, and the study flow diagram is presented in Figure 1. The SPIRIT 2025 checklist is provided in Table S1 (Supplementary Materials). The study protocol was registered at ClinicalTrials.gov (NCT07446062). Recruitment began in February 2026 and is estimated to be completed in March 2027.

### 2.3. Settings and Participants

The intervention will be delivered in a home-based format at each participant’s home. Participants will be included if they have been diagnosed with ischemic or hemorrhagic stroke at least 6 months before enrolment [31], are aged between 20 and 80 years [31], are able to walk at least 10 m with or without assistive devices [32], are able to perform sit-to-stand safely with or without assistive devices, can see the screen of a tablet or notebook computer at a distance of at least 60 cm [33], have a stable medical condition and are able to follow study instructions [32], and are frequent users of a mobile phone, tablet, or notebook computer. Participants will be excluded from the study if they have medical conditions or complications that would be unsafe to exercise [31], have neglect, impaired communication, or uncorrected visual problems [32], or have severe spasticity of the upper or lower extremities (Modified Ashworth Scale ≥ 3) [31,32].

### 2.4. Participant Characteristics

Participant characteristics including age, body mass index, gender, and education level will be recorded. Medical information regarding stroke characteristics, including stroke type, paretic side, and time since stroke onset will also be collected.

### 2.5. Sample Size

The sample size was calculated using G*Power version 3.1.9.2 based on outcome measures. Effect sizes were derived from previous studies, which reported values of 0.46 for executive function [34], 0.57 for fall risk [35], and 0.37 for gait speed [36,37]. With a power of 0.80 and an alpha level of 0.05, sample sizes of 30, 20, and 46 will be required to detect a change in executive function, fall risk, and gait speed respectively. Accordingly, a total sample size of 46 participants is considered sufficient to detect changes in outcome measures. To accommodate a 10 percent dropout rate, a total of 52 participants (26 per group) will be enrolled in the study. However, the appropriate sample size will be recalculated using data from our preliminary study.

### 2.6. Randomization and Allocation Concealment

Eligible participants will be randomly allocated to the intervention or control group in a 1:1 ratio. Randomization will be performed by an independent researcher using a computer-generated randomization sequence created with SPSS version 25. Allocation concealment will be ensured using sealed, opaque, and sequentially numbered envelopes, which will be opened only after baseline assessment and participant enrolment. All outcome assessments will be conducted by trained assessors who are blinded to group allocation. Due to the nature of the intervention, neither the physiotherapist delivering the intervention nor the participants can be blinded.

### 2.7. Procedure

Participants will be recruited through both online and offline advertisements within local communities. Written informed consent will be obtained from eligible participants before participation in the study. All participants will be assessed for physical function (motor function, gait speed, balance and limits of stability, fall risk, muscle power, and weight distribution) and cognitive performance (global cognitive function, executive function, memory, and attention). Physical and cognitive performances will be assessed at baseline and after the end of 12 weeks of intervention. The enjoyment rating scores will be determined after 1 week and 12 weeks of training. A 12-week home-based training program will be implemented in this study. Participants will be encouraged to contact the research team whenever they have questions or concerns.

### 2.8. Interventions

#### 2.8.1. Web-Based Physical–Cognitive Telerehabilitation Exergaming

Participants will perform a physical–cognitive exergame via ExerbrainCMU web-based platform at home setting for 60 min/session, 3 sessions/week for 12 weeks. The program will consist of warm-up, physical–cognitive training, and followed by cool-down. The physical–cognitive exergame will consist of trunk exercises, upper- and lower-extremity exercises, exercises using Proprioceptive Neuromuscular Facilitation (PNF) patterns, balance exercises, aerobic exercises, sit-to-stand training, and side-walking exercises, combined with cognitive training targeting executive function, attention, memory, visuospatial ability, and dual-task performance. In general, physical–cognitive exergames will mostly be performed in a sitting position. Task difficulty will be progressively increased by manipulating movement complexity, speed, and directional demands, while cognitive load will be adjusted by varying cognitive complexity, the number of stimuli, task conditions, attentional demand, and memory load. The intervention will comprise three difficulty levels: easy (weeks 1–4), medium (weeks 5–8), and hard (weeks 9–12). Participants scoring below 80% across all games will be required to repeat the current level until the 80% passing criterion is met before progressing to the next level. Instructional materials, including basic instructions and training videos, will be provided to ensure correct and safe execution of the intervention. A summary of the intervention is presented in Figure 2 and Table S2 (Supplementary Materials).

Telerehabilitation will be conducted using the ExerbrainCMU web-based platform. Participants will engage in exercise training at home or in remote areas via simultaneous video conferencing, accompanied by a physiotherapist. The telerehabilitation system consists of a main monitoring controller for physiotherapists, a network data system, and connected end-users who are stroke patients. The main monitoring controller enables therapists to monitor exercise accuracy and safety at weeks 2, 4, 8, 10, and 12. Family members or caregivers may stand beside participants if there are safety concerns.

Prior to commencing the 12-week home-based intervention, participants will practice the exercises under the supervision of a physiotherapist to ensure proper and safe performance. During training, participants will be instructed to monitor their own fatigue, RPE, and movement performance (e.g., task accuracy, movement quality, and completion of prescribed tasks). The RPE will be self-reported and recorded, with target intensities of 12–14 for Levels 1–2 and 15–17 for Level 3. Participants will be advised to reduce the intensity of the exercise, contact the researcher, or terminate the session according to predefined safety criteria if they experience excessive fatigue (e.g., RPE above the target range), discomfort, dizziness, or difficulty maintaining postural stability. Participants will also receive a booklet to record their training activities and any adverse events.

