#### 2.8.2. Control Condition

Participants in the control group will continue their usual lifestyle or receive usual care rehabilitation during the study period, with no additional intervention. They will be encouraged to maintain their usual activities and avoid participation in other structured exercise programs outside the study intervention. The type, frequency, and intensity of concurrent treatments will be recorded and treated as covariates in the statistical analysis to control for potential confounding effects. After the 12-week period, they will be invited to participate in the intervention program according to their preference. Participants will be asked to inform the research team if there are any routine changes or unexpected events (e.g., hospital admission, illness).

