### 2.9. Intervention Adherence and Adverse Events

Participants in the intervention program will have their training sessions automatically recorded on the ExerbrainCMU web-based platform immediately after each exercise session, including information on session duration, training completion, and training frequency. These data will be used to monitor adherence and engagement throughout the intervention period. Weekly reminders will be sent via social media applications (e.g., LINE and Facebook) to promote adherence. In addition, research staff will conduct scheduled telemonitoring sessions at weeks 2, 4, 8, 10, and 12, during which information regarding participants’ training will be collected and cross-validated with the platform records.

Participants will be instructed to report any adverse events that occur during the study. They will also be asked about any health problems at each assessment point from baseline to 12 weeks. Participants will be informed that they can contact the research team at any time if they have questions or concerns. All adverse events or harms associated with the intervention will be recorded and reported in the study findings.

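### As described, adverse events are sought more intensively in the exergame arm than in controls, and the reporting sentence can be read as omitting unattributed events, so counts by arm are open to detection bias

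*Protocol article*

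**What the plan says.** **Exergame arm.** Section 2.8.1 states that "Participants will also receive a booklet to record their training activities and any adverse events". It also says: "The main monitoring controller enables therapists to monitor exercise accuracy and safety at weeks 2, 4, 8, 10, and 12". Section 2.9 lists sessions in the same five weeks and gives their content differently: "research staff will conduct scheduled telemonitoring sessions at weeks 2, 4, 8, 10, and 12, during which information regarding participants’ training will be collected". For symptoms during training, section 2.8.1 adds: "Participants will be advised to reduce the intensity of the exercise, contact the researcher, or terminate the session according to predefined safety criteria".

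**Control arm.** Section 2.8.2 says: "Participants will be asked to inform the research team if there are any routine changes or unexpected events". Its examples are a hospital admission and an illness. No booklet and no scheduled contact between baseline and week 12 is described.

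**No arm restriction stated.** Section 2.9 says: "Participants will be instructed to report any adverse events that occur during the study". It also provides for a question on health problems at every assessment point and an open line to the research team. Sections 2.7 and 2.10 and Table 1 place the physical and cognitive assessments at baseline and week 12.

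**Reporting.** Section 2.9 ends: "All adverse events or harms associated with the intervention will be recorded and reported in the study findings".

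**The concern.** When one arm keeps a running record and meets staff five times, and the other must volunteer events or recall 12 weeks at a single visit, minor events will probably be recorded more completely in the first arm. A difference in counts then mixes any true effect of training with the effect of looking harder. This can mislead in two ways: home training may look more harmful than it is, or a real excess may be dismissed as an artefact of ascertainment.

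The question matters in this trial. Participants are stroke survivors, fall risk is a primary outcome, and the training includes balance, sit-to-stand and side-walking work at home. Readers will want to know whether the programme is safe relative to usual care. The article commits to publishing harms, so the arms are likely to be set side by side even though no test is planned. No later analysis can recover events that were never elicited.

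The reporting sentence is a second, separate difficulty. If the phrase about association with the intervention governs both nouns, control events drop out of the report, as do exergame-arm events judged unrelated. The article states no method for that judgement.

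**Working it through.** The plan gives no adverse-event rate and no harms comparison, so there is no stated figure to reproduce. The check is a count of ascertainment occasions, followed by an illustration of scale.

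**Step 1. Occasions after randomisation, as described**

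| Route | Exergame | Control | Source |
|---|---|---|---|
| Adverse-event booklet | Yes | Not described | 2.8.1 |
| Scheduled staff sessions | 5 | 0 described | 2.8.1, 2.9 |
| Advice that includes contacting the researcher for symptoms | Yes | Not applicable | 2.8.1 |
| Health-problem question at week 12 | 1 | 1 | 2.7, 2.9, Table 1 |
| Spontaneous report of any event; open contact | Yes | Yes | 2.7, 2.9 |
| Request to report unexpected events | Covered by the row above | Yes | 2.8.2 |

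The baseline enquiry precedes allocation (section 2.6), so it cannot capture events under treatment. The week-1 enjoyment rating might count as a further assessment point. It concerns enjoyment of the training, so it appears to apply to the exergame arm only. It is left out of the count.

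**Step 2. What unequal capture does**

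Inputs: 26 per arm (section 2.5). True risk of at least one event *p* and capture probabilities *c*E (exergame) and *c*C (control) are assumptions. The true risk is set equal in both arms.

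- Expected participants with a recorded event = 26 × *p* × *c*
- Spurious risk ratio = *c*E / *c*C, in which *p* cancels
- Spurious risk difference = *p* × (*c*E − *c*C)

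With *p* = 0.30:

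| *c*E / *c*C | Exergame | Control | Risk ratio | Risk difference |
|---|---|---|---|---|
| 0.90 / 0.70 | 26 × 0.30 × 0.90 = 7.0 | 26 × 0.30 × 0.70 = 5.5 | 1.29 | 0.30 × 0.20 = 6 points |
| 0.90 / 0.50 | 7.0 | 26 × 0.30 × 0.50 = 3.9 | 1.80 | 0.30 × 0.40 = 12 points |
| 0.80 / 0.40 | 26 × 0.30 × 0.80 = 6.2 | 26 × 0.30 × 0.40 = 3.1 | 2.00 | 12 points |
| 0.90 / 0.90 | 7.0 | 7.0 | 1.00 | 0 points |

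For 0.90 against 0.50, the risk difference runs from 0.20 × 0.40 = 8 points at a true risk of 20% to 0.50 × 0.40 = 20 points at 50%.

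**Step 3. The reporting sentence, read both ways**

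- *The qualifier covers both nouns.* Only intervention-associated events are reported. Controls contribute none, and there is no background rate against which to judge the exergame arm.
- *The qualifier covers only harms.* All adverse events are reported, but from the unequal ascertainment in Step 1.

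Either reading leaves a problem, and the sentence does not settle which is meant.

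**The case against.** The strongest case against the point has five parts.

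- **The five sessions.** A reader might infer that they are adverse-event enquiries. The article does not say so. Section 2.9 gives their content as training information, checked against platform records; only the word safety in section 2.8.1 points further, and it may mean supervision of the exercises. This stands. The sessions are still live staff contacts that controls are not described as having, and the booklet creates an asymmetry without them.
- **Controls' other routes.** A reader might infer that controls are heard only once. That is true only of scheduled enquiry after randomisation. Controls are also told to report any adverse event, asked to report unexpected events, and may call at any time. This stands, and it could narrow the gap. But spontaneous reporting is open to both arms, so it does not replace the exergame arm's extra prompts.
- **No comparison is planned.** Adverse events are neither a primary nor a secondary outcome, and section 2.11 contains no test of them. This stands. It limits the consequence to descriptive counts, which readers will nevertheless compare.
- **The reporting sentence.** The qualifier may attach only to harms, and the same paragraph asks for any adverse event. This stands: the sentence is ambiguous, and it cannot be called a definite restriction. Nor does the article support an inference that unblinded staff would judge attribution, since it names no judge.
- **A condensed article.** The booklet may be listed under the intervention because it doubles as a training log, and the full protocol may give controls an event record. Section 2.8.2 does provide for recording concurrent treatments, without saying how. This is possible and would remove part of the point. But the article does set out adverse-event methods, and what it sets out differs by arm.

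**Conclusion.** The point holds in a limited form. As described, scheduled ascertainment after randomisation is a booklet, five staff sessions and a week-12 question in the exergame arm, against the week-12 question in controls, with spontaneous reporting in both. Adverse-event counts by arm are therefore open to detection bias, most likely towards over-counting in the exergame arm. Separately, the reporting sentence needs a single meaning.

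The size cannot be established from the article. The spurious ratios of 1.3, 1.8 and 2.0 are each one assumed capture rate divided by another; they show scale and do not estimate the bias. If spontaneous reporting made capture equal, the ratio would be 1.0.

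A reader might go further and conclude that harms cannot be compared fairly at all. The document does not support that: the extent of the bias is unknown, a common week-12 enquiry exists, and no formal between-arm comparison is proposed. The weakness is worth correcting because the remedy is cheap and has to be applied while events are being collected.

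**What to change.** 1. Give both arms the same adverse-event page, with falls listed explicitly, separate from the training log.
2. Ask both arms the same brief adverse-event question on the same schedule. The existing session weeks (2, 4, 8, 10 and 12) would serve. State in section 2.9 that the exergame sessions include this question.
3. Reword the last sentence of section 2.9 so that all adverse events are recorded and reported by arm regardless of attribution, with intervention-related events as a subset.
4. If the enquiry is not equalised, limit the between-arm presentation to events elicited by the common week-12 enquiry, and describe booklet or session events for the exergame arm only.

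**Cost.** One page and five short contacts for each of 26 controls, or 5 × 26 = 130 contacts. The messaging reminders in section 2.9 are described as promoting adherence to training, so a route to controls may need to be set up. Controls would have slightly more contact than now, in a condition defined as having no added intervention. Recruitment began in February 2026, so the change should be made promptly and its date recorded, because participants already followed will have been under the unequal schedule.
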